
### Brain dynamics

To examine the changes in brain dynamics induced by the three intervention techniques, all patients perform simple unimanual and bimanual force production tasks with their hands, while whole-head MEG recordings will be made (CTF Systems Inc., Vancouver, Canada and Elekta Neuromag, Stockholm, Sweden). Task performance (i.e., onset and displacement of hand squeezes) will be monitored by pump bulbs (RXPUMPBULP, BIOPAC Systems, Inc., Goleta, CA, USA), tubing, and pressure transducers. The to be performed task will be as follows: 2 min of rest, 30 s of rhythmic squeezing on auditory cues, 30 s of rest, 30 s of rhythmic squeezing on auditory cues, 30 s of rest, 30 s of rhythmic squeezing on auditory cues, and finally 2 min of rest. Hence, the duration of a single task will be 6 min and 30 s. The frequency of auditory cues will be set at 1 Hz. The task will be performed once with the left hand only, once with the right hand only, and once bimanually. Surface EMG will be applied (using data acquisition channels built into the MEG system) to monitor task performance.

The MEG signals will be mapped from sensor space to source space using the synthetic aperture magnetronomy (SAM) minimum linear variance beamforming approach [97] to determine the brain regions that show the largest contrast when comparing activity pre- and post performance [98]. Changes in power in various frequency bands (theta, alpha, beta, and gamma) and cortico-cortical synchrony (using instantaneous Hilbert phase and the phase locking index; [99]) in these bands will be examined. For the associated analyses see Houweling et al. [98].

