Functional MRI studies and TMS studies already indicated that, during paretic arm movement, CIMT results in increased metabolic activation in the primary sensorimotor cortex of the affected hemisphere [50-62], whereas BATRAC results in increased metabolic activation in the contralesional cerebrum and ipsilesional cerebellum [20,21].

Modified CIMT is hence expected to result primarily in changes in ipsilesional hemisphere functioning, i.e., greater activity in the primary sensorimotor cortex of the affected hemisphere and increased phase synchronization between regions surrounding the lesion (we note that assessing the latter requires the high temporal resolution of encephalographic recordings), which may be related to restitution of its former functionality. In contrast, modified BATRAC is expected to primarily induce adaptations in the contralesional hemisphere, enhanced activity in the (ipsilesional) cerebellum (possibly reflecting enhanced timing abilities), and a considerably greater increase in the degree of phase synchronization between the lesioned hemisphere and the contralesional hemisphere than will occur as a result of either modified CIMT or DMCT. This finding would indicate compensatory cortical reorganizations in which the coupling to the nonaffected hemisphere acquires a special role in the motor control of the paretic arm.

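### The MEG phase locking index between beamformed sources does not separate leakage and source-power effects from true coupling, above all for the intrahemispheric CIMT prediction

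*Protocol article*

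**What the plan says.** Brain dynamics (Methods) has the MEG signals "mapped from sensor space to source space using the synthetic aperture magnetronomy (SAM) minimum linear variance beamforming approach", in order "to determine the brain regions that show the largest contrast when comparing activity pre- and post performance". It then plans two kinds of measure in the same bands. One is power: "Changes in power in various frequency bands (theta, alpha, beta, and gamma"). The other is coupling: "cortico-cortical synchrony (using instantaneous Hilbert phase and the phase locking index; [99]) in these bands will be examined". No direction is given for the power change. No leakage-insensitive measure and no control for power is described. Further detail is left to cited work ("For the associated analyses see" reference 98), which is not available here.

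The Background states what the synchrony results should show. For modified CIMT it expects greater activity in the primary sensorimotor cortex of the affected hemisphere together with "increased phase synchronization between regions surrounding the lesion". For modified BATRAC it expects adaptations on the contralesional side, more activity in the ipsilesional cerebellum, and "a considerably greater increase in the degree of phase synchronization between the lesioned hemisphere and the contralesional hemisphere" than under the other two treatments. It would take that last result as a sign of compensatory reorganisation.

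The section Associated mechanisms places MEG among three additional tests. MEG is neither the primary outcome (ARAT) nor one of the secondary outcomes listed under Outcome variables.

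**The concern.** The phase locking index is the length of the average phase-difference vector. It counts any stable phase relation as locking, including the zero-lag relation that arises when one source leaks into the estimate of the other. Beamformed signals carry some such cross-talk, most of it between neighbouring regions. Noise in the estimates pulls the index down, so a change in signal-to-noise also moves it.

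If an arm changes source power, its index can therefore change with no change in coupling. The modified CIMT prediction is the most exposed. It expects more activity and more synchrony in the same hemisphere and among nearby regions, so support for the first could look like support for the second. At stake is the second research question, on how functional change relates to cortical networks.

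**Working it through.** The article prints no figure on this point, so there is none to reproduce. The check sets true coupling to zero, or holds it constant, and looks at what the index does.

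**Inputs from the article.** Hilbert phase, phase locking index and a minimum-variance beamformer. Each task has three blocks of "30 s of rhythmic squeezing on auditory cues", so 3 × 30 s = 90 s.

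**Assumptions.** The standard index |mean exp(iΔφ)|, a 15–30 Hz band, leakage fraction k, unit noise, size of the power change, head geometry and beamformer regularisation. None of these is in the article.

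**Step 1: leakage without coupling.** Take two independent sources of power A, symmetric zero-lag leakage k and unit noise. The correlation of the two estimates is

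ρ = 2kA / [A(1 + k²) + 1],

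and for Gaussian signals the index is (π/4)·ρ·F(½,½;2;ρ²), roughly (π/4)·ρ·(1 + ρ²/8).

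- k = 0.2, A = 1: ρ = 0.4/2.04 = 0.196, index 0.155.
- k = 0.2, A = 4 (amplitude doubled): ρ = 1.6/5.16 = 0.310, index 0.247.

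Simulation of 90 s agrees:

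| Leakage k | Index, A = 1 | Index, A = 4 |
|---|---|---|
| 0.1 | about 0.08 | about 0.12 |
| 0.2 | about 0.15 | about 0.25 |
| 0.3 | about 0.23 | about 0.36 |

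Without leakage the index is about 0.02, the finite-sample floor. The phase lag index and the absolute imaginary coherency stay at 0.01–0.02 in all these leakage cells.

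**Step 2: direction under a beamformer.** The simulation used a spherical head model, 275 gradiometers, 4 mm location error, and four background levels with regularisation of 0 or 5%, so eight settings. True coupling was zero.

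- Within a hemisphere (sources 2.4 cm apart) the index was 0.08–0.22. With all powers up 4-fold and weights recomputed, it rose in 7 of 8 settings (for example 0.115 to 0.159) and fell in one (0.098 to 0.085). With weights held fixed, it fell in 7 of 8 (for example 0.115 to 0.078).
- Between hemispheres (8.0 cm apart) it was 0.01–0.05, and the change with power was at most about 0.024 either way, close to the floor.
- In simple mixing with k = 0.2 and no noise, raising both powers equally left the index at 0.309.

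**Step 3: constant true coupling.** With no leakage and a shared-variance fraction of 0.4, ρ = 0.4·A/(A + 1).

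- A = 0.5: ρ = 0.133, index 0.11.
- A = 4: ρ = 0.32, index 0.25.

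In one beamformer setting with true coherence 0.3 and recomputed weights, the between-hemisphere index instead fell from 0.137 to 0.108 as power rose 4-fold.

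**Step 4: is a lag-based measure enough?** Take the same shared fraction of 0.4, a 12 ms lag, no leakage and unit noise. Doubling the amplitude raised the phase lag index and the imaginary coherency from about 0.19 to about 0.30, and the phase locking index from 0.15 to 0.24. A lag-based measure removes the leakage problem but not the signal-to-noise problem.

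**The case against.** The strongest reply is that the article defers the analyses to reference 98 and condenses a fuller protocol, so leakage or power control may be specified there. That stands as far as it goes: a reader might infer that no safeguard exists, and the article cannot show that. But the choice of index is stated in the article, and so are the coupling conclusions to be drawn from it.

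A reader might also infer that the index always rises with power, so that any predicted activity increase would produce the predicted coupling increase. Step 2 does not support this, because the direction depends on weights, noise and regularisation. Nor does the article equate greater activity with higher band power.

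Third, a reader might carry the concern over in full to the interhemispheric BATRAC prediction. The simulated leakage there is small, and the activity increase named for BATRAC is cerebellar, not in the two hemispheric sources whose coupling is predicted to rise. Signal-to-noise dependence remains, without a fixed direction.

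Finally, power is to be examined in the same bands, so a concurrent power change would be visible. Seeing it is useful, but the article does not say that it would enter the reading of the synchrony result.

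**Conclusion.** The point holds in limited form. An index that is non-zero without coupling, and that moves either way when power changes, cannot by itself support a conclusion about changed coupling. It could equally mask a real change.

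The size is material for neighbouring regions, with a spurious index of 0.08–0.22 in the beamformer simulation. Between hemispheres it is small, at 0.01–0.05. The modified CIMT prediction is thus the one most in need of protection. These values rest on the assumed leakage, noise, geometry and power change; they show that the effect is plausible and do not estimate it for this trial. The ARAT comparison and the efficacy conclusions are unaffected.

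**What to change.** Keep the phase locking index. For the same region pairs and bands, report beside it a leakage-insensitive measure, either the phase lag index or the imaginary part of coherency. Adjust the change in both measures for the change in source power in both regions.

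Attribute an arm difference to changed coupling only if two conditions are both met: the leakage-insensitive measure changes, and that change remains after the power adjustment. Step 4 shows why meeting one of them is not enough. If reference 98 or the full protocol already provides for this, a sentence in the plan saying so would settle the point.

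The cost is a little more analysis of data that will be recorded anyway, with no new patients or procedures. The drawback is that lag-based measures miss true zero-lag coupling. A change seen only in the phase locking index would have to be reported as not distinguishable from leakage.

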## Discussion

The ULTRA-stroke program is expected to have a strong impact on the treatment policies for stroke survivors. Given that about 80% of all stroke victims show upper limb paresis immediately following stroke [4], hampering unimanual and bimanual coordination [5], and the fact that only one third of all stroke patients will regain some dexterity within six months with conventional treatment programs [7], a sufficiently powerful RCT investigating the effectiveness of innovative therapies is relevant and urgently needed to objectively guide stroke rehabilitation.

Specifically, the combination of assessments of effectiveness and mechanisms associated with intervention-induced functional improvement will prove to be valuable for clinical practice. Therefore, next to the effectiveness of modified BATRAC and modified CIMT, the ULTRA-stroke program also intends to investigate how longitudinally changes in (a) upper limb neuromechanics (i.e., peripheral stiffness and interlimb interactions), and (b) neuroplasticity (i.e., changes in cortical inter- and intrahemispheric networks), are associated with recovery of motor impairment (i.e., synergism and strength) and upper limb function (i.e., dexterity). The outcome of the RCT, together with information about longitudinal changes in the underlying mechanisms of upper limb recovery, will provide clinicians a tool to make appropriate decisions in selecting evidence-based therapies for the paretic upper limb.

The ULTRA-stroke program is contingent upon the fact that the major part of post-stroke rehabilitation treatment takes place during the subacute phase. Since 2006, meta-analyses have shown that CIMT is an effective way to improve upper limb function in chronic stroke patients [18,27-29]. The same applies to BATRAC [19,20,100] (but see also [101]). However, high quality RCTs pertaining to the subacute phase post stroke have thus far been lacking in the literature [102]. Consequently, the ULTRA-stroke program is a unique and innovative project in stroke rehabilitation science.

As stated before, a better understanding of how specific therapies influence neurobiological changes, and more important, what post-stroke conditions lend themselves to specific treatments, will help clinicians to tune the treatment to the needs of the individual patient. The knowledge gained in the ULTRA-stroke program will further underpin the concepts of motor recovery and motor learning in stroke rehabilitation by addressing the key question: what changes in underlying mechanisms are associated with functional improvement after stroke?

Results of the ULTRA-stroke program are expected at the beginning of 2012.
